#### Randomization and sample

The PI utilized a random numbers table to generate the random allocation sequence. The PI has the list of condition by case number and did not share the sequence with any team member. The condition was identified on a sheet of paper within the initial enrollment packet, and all study personnel were trained not to examine the condition before enrolling a transition-age youth and their family.

We will recruit 60 transition-age youth with SMHC and approximately 20 stakeholders. The sample size is typical for the pilot nature of this research. The National Institutes of Health (NIH) grant mechanism under which this proposal was funded (R34) is intended for intervention feasibility and acceptability testing, and therefore we will conduct only exploratory statistical testing of study outcomes. Our primary goal in this proposal is to gather preliminary data regarding feasibility and acceptability of our intervention to inform a future large-scale, fully powered, randomized control trial of Cornerstone. Given the intended pilot nature of this research and our modest sample size, which is due to the logistical constraints of the grant mechanism, conducting formal tests of outcomes or attempting to obtain an estimate of an effect size is not typically recommended. Still, with our sample size of 30 per group we will have 80 % power with *p* = 0.05 to detect a large effect of the intervention (Cohen’s d = 0.73).

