### Recruitment, informed consent, inclusion/exclusion criteria, and sample

#### Recruitment

An established and respected mental health agency has agreed to partner to execute the proposed project. In addition, we will draw on the resources of the National Council of Behavioral Health, Inc. and affiliated research centers. The agency will receive information about Cornerstone and materials to provide to their clients who meet inclusion criteria about participation. The PI and the project coordinators will oversee recruitment and informed consent procedures. The agency will partner with research staff to develop a list of potential participants, who meet inclusion criteria. Potential participants and their caregivers/guardians will be approached by their service provider to introduce the study. The relationship already established with their providers will protect confidentiality and providers are in the best position to assess appropriateness for the Cornerstone project, particularly with the new protocols that will be developed for ‘phasing in and out’ participants of Cornerstone. The project will be presented, including procedures for randomization and confidentiality. Then, if interest is shown, the provider will ask for verbal consent for the research staff to contact the potential participant. Research staff will explain the project and, if appropriate, go through the consent process. Both the young person and their caregiver will need to give consent/assent if the potential participant is not an adult or is not capable for consenting for themselves.

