### Interview protocol

#### Timing of assessment and procedures

All participants will be interviewed by the research team at four time points: baseline (beginning of intervention), 3 months, 6 months, and post-test (approximately 9 to 12 months after baseline). The baseline and final interview will last approximately 90 minutes (compensation for participants time is $20/assessment) and the 3-month and 6-month follow-ups will last approximately 60 minutes. The interviews consist mainly of self-report questionnaires with some open-ended questions. The importance of honest responding will be stressed and a measure of social desirability response tendencies will be included for use as a covariate. There is debate about whether interviewer-administered questionnaires yield as truthful responses. If respondents are assured confidentiality, there is evidence to suggest that the differences in the two methods of assessment are minimal (e.g., [45]). Cornerstone participants will complete the assessments in planned meetings at the clinic. Structured and intensive interviewer training for the research staff will be conducted based on a training protocol. We estimate the training to require 8 hours of direct instruction and 4 hours of practice. Interviewer training will cover the following: (a) the research process and the clinic setting, (b) federal law regarding informed consent and the rights of research participants, (c) the basics of interviewing and the specifics of the project interview schedule, (d) coding interviews, (e) managing participant discomfort during and after an interview, (f) education about topics such as the psychosocial effects of poverty, trauma, mental illness and treatment, (g) desensitization to discussing poverty, trauma and mental illness, (h) interviewing participants from diverse cultural backgrounds, and (i) psychiatric interviewing. Then, weekly follow-up research staff meetings will be utilized to reinforce training and provide support throughout the trial.

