### Ethical issues and dissemination

The RCT protocol for all research aims has been reviewed and approved by the New York University Committee on Activities Involving Human Subjects as of November 30^,^ 2016 (IRB-FY2016-172). For protocol modifications the research team will submit an amendment to the Committee on Activities Involving Human Subjects. Consent (and assent for those under 18) to enroll in the study will be processed and obtained by the PI or trained project research staff who have all been trained on activities involving human subjects.

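### Allocation is not adequately concealed: the PI holds the list and may take consent, and the condition sheet is already in the enrolment packet

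*Protocol article*

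**What the plan says.** Randomization and sample, in the protocol article, describes the whole mechanism. On generation: "The PI utilized a random numbers table to generate the random allocation sequence". On custody: "The PI has the list of condition by case number and did not share the sequence with any team member". On where each assignment sits before use, and who was told not to look: "The condition was identified on a sheet of paper within the initial enrollment packet, and all study personnel were trained not to examine" it too early. The safeguard in full: "all study personnel were trained not to examine the condition before enrolling a transition-age youth and their family".

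Two other sections place the PI in the enrolment pathway. Recruitment states: "The PI and the project coordinators will oversee recruitment and informed consent procedures". Ethical issues and dissemination says that consent, and assent for minors, "will be processed and obtained by the PI or trained project research staff".

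Trial status reports 30 participants enrolled, out of the planned 60 (30 per group).

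**The concern.** Concealment means that nobody who can influence whether, when or how a person enters the trial can know the next assignment. Here the person who made and keeps the list can also enrol. That person also helps supervise the Cornerstone providers, according to Recruitment, screening, training, and supervision. For the remaining staff, the assignment is already in the packet used for enrolment, so concealment depends on compliance with an instruction.

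There is some room for discretion at that point. Under Recruitment, research staff explain the project and go on to consent if they think it appropriate. With foreknowledge, a young person thought likely to do well could be encouraged, delayed or passed over according to the arm that comes next. If that happened, the arms would differ in expected change for reasons other than treatment. The unadjusted t test on change from baseline, described under Analysis, would count the difference as treatment effect. The preliminary impact data are meant to inform a larger trial, and the same procedure could be carried into it.

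**Working it through.** **Step 1. Who can know the assignment, and who can act on it**

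| Function | Who | Where stated |
|---|---|---|
| Generates the sequence | PI | Randomization and sample |
| Holds the list by case number | PI only | Randomization and sample |
| Oversees recruitment and consent | PI and project coordinators | Recruitment |
| Obtains consent | PI or trained research staff | Ethical issues and dissemination |
| Judges appropriateness when introducing the study | Agency service provider | Recruitment |
| Condition sheet before enrolment | In the enrolment packet | Randomization and sample |

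The PI appears in both the knowing and the enrolling rows. Withholding the list from the team does not help with anyone the PI enrols. For research staff, withholding the list protects little, because each single assignment is already in the packet. An instruction not to examine the sheet matters only if the sheet could be examined. The article mentions no seal, independent holder or central release.

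**Step 2. The only design figure nearby**

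The article gives 80% power at p = 0.05 for d = 0.73 with 30 per group. Taking the test as two-sided (sidedness is not stated):

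- Normal approximation: 0.73 × √(30/2) = 0.73 × 3.873 = 2.827. Then 2.827 − 1.960 = 0.867, giving power of 80.7%.
- Noncentral t: 79.4%.

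The stated figure reproduces. The concealment point does not depend on it.

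**Step 3. What an entry difference would do (assumed inputs)**

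The article has no data on selection, so the following is illustration only. Let b be the difference between arms in expected change, in SDs of the change score, caused by selection alone with no treatment effect. With 30 per group (58 degrees of freedom) the noncentrality is b × √15, and the two-sided 5% t test rejects as follows:

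| Assumed b (SD of change) | Noncentrality | Rejection rate |
|---|---|---|
| 0 | 0 | 5.0% |
| 0.1 | 0.387 | 6.7% |
| 0.2 | 0.775 | 11.9% |
| 0.3 | 1.162 | 20.8% |

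The unit matters. A young person who is stably better at both baseline and 9 months contributes nothing to b, because the level cancels in the change score. Only selection on likely improvement counts.

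**Step 4. Could a before/after comparison detect bias in the first 30?**

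Suppose the procedure changes halfway, with about 15 per arm in each period (assumed; the split so far is not reported). In SD units, each period's effect has variance 2/15. The difference between the two effects has SE √(2/15 + 2/15) = √(4/15) = 0.52, and a 95% half-width of 1.96 × 0.52 ≈ 1.0 SD. A shift of 0.2 SD would be invisible.

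**The case against.** The strongest reply has four parts.

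- **The PI's part may be small.** Recruitment has the agency and research staff build the candidate list, the provider introduce the study and research staff explain it. The PI is one possible consenter, not the only one. This stands. A reader might infer that the PI judges eligibility, but no section says so. The appropriateness judgement belongs to agency providers, and nothing suggests they saw the list.
- **There are safeguards.** The list was withheld from the team, staff were trained not to look before enrolling, and the sheet may have been sealed. This also stands, and for that reason the claim is inadequate concealment, not absent concealment. Even a seal would leave the PI's own knowledge untouched.
- **The article condenses a fuller protocol.** That would excuse missing detail, but here the article describes the mechanism itself, and the mechanism is weak. The excuse does apply to one tempting extension. Baseline is labelled "baseline (beginning of intervention", and a reader might infer that baseline answers are given with the arm known. The label only marks a time point. The order of interview and disclosure is a detail an article may leave out, so the inference is not supported.
- **This is a pilot.** Feasibility and acceptability are the primary goal, and outcome testing is called exploratory. This lowers the severity. It does not remove the point, because Aim 2 still compares the randomised arms for preliminary impact.

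**Conclusion.** The concern holds in this form: allocation is not adequately concealed, because the PI both holds the list and may enrol, and because the condition sheet sits in the packet with training as the only stated barrier to looking. It rests on stated text and assumes only that the PI does sometimes take consent and that staff handle the packet before enrolment is final.

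The documents show that selection is possible. They do not show that it occurred, and they give no basis for estimating its size; the rejection rates in the table are conditional on assumed differences. Two stronger readings should be avoided:

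- **A bias of a fixed size, taken from youth who are better or worse at entry.** Stable level differences cancel in the change scores, and regression to the mean could even work against Cornerstone.
- **That every outcome is subjective and so open to the same distortion.** The measures table includes attendance sheets, clinician-reported adherence, housing and insurance, and the abstract adds medical records.

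Severity is moderate.

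**What to change.** For participants still to be enrolled:

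1. Take the condition sheet out of the enrolment packet.
2. Have a person with no part in recruitment or consent generate the remaining assignments, unseen by the PI. Set the numbers per arm so that the final totals reach the planned 30 per group, given the split so far.
3. Place the assignments in sequentially numbered, opaque, sealed envelopes. Open each one only after consent and the baseline interview are complete and the ID is in the tracking form.
4. Have consent taken only by the trained research staff already named, not by the PI.

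In the report, state how the first 30 were allocated, including who consented them and whether the sheet was sealed, and disclose this as a limitation. Do not present a before/after comparison as a test of bias, for the reason in Step 4.

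The cost is a short procedure memo, envelopes and an IRB amendment, for which the article already gives the route. Research staff already take consent, so that step adds no post. An uninvolved person must be found to prepare the envelopes, and the article does not name one. Because the remaining numbers per arm are fixed, the last few assignments could be guessed by anyone keeping a tally, so the running split should be kept from those who enrol as far as practicable. If enrolment has moved past 30, the change protects fewer participants and disclosure carries more of the weight.

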### Enrollment, retention, and tracking

The names and identification numbers (IDs) of participants who consent to become involved will be entered into a tracking form. IDs will be substituted for names on all questionnaires and study forms. Confidentiality of data will be assured by maintaining locked file cabinets and protected electronic files that require a password. The PI and project coordinators will be responsible for maintaining IDs and data files. We have created a tracking system using established strategies [43]. The investigative team has considerable experience with recruitment and retention of transition-age youth with serious mental health conditions in a variety of settings, and with individuals in poverty experiencing multiple stressors. Our strategies have resulted in high retention rates (90 %) in our previous studies [4, 44]. We will use these experiences to implement the tracking system and to help minimize logistical barriers for participation. Furthermore, some of the young people targeted for enrollment will already be receiving care at the clinic. Due to the close relationship between the staff and the investigators, we anticipate few participants will be lost to follow-up. Keeping a list of participant names, addresses, phone numbers, and contacts will enable us to make phone calls and send appointment reminders in an effort to maintain engagement. We will also ask each participant on a regular basis to update their phone numbers and addresses so that we have alternative ways of reaching them. This tracking system will be locked in a separate file cabinet from all study data that will only be identified by a study ID number. Based on our experiences, we do not anticipate many participants will be lost due to relocation. We are recruiting 60 transition-age youth (TAY) to achieve a final sample size of 55.

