Data analysis for aim 2: due to limited sample size we will proceed cautiously to conduct basic omnibus analyses to examine whether Cornerstone leads to improved outcomes relative to TAU, as this study is intended for intervention feasibility and acceptability testing, and therefore we will conduct only exploratory statistical testing of study outcomes. Our primary goal in this proposal is to gather preliminary data to inform a future large-scale, fully powered, randomized control trial of Cornerstone [51]. For each study subject we will calculate the difference, relative to baseline, at the end of the study for each outcome specified (see Table 2 above). A simple *t* test will be used to assess whether these changes differ across treatment conditions. For example, we will examine whether the mean within-person difference between the 9-month assessment and baseline assessment of intention to use services differs for subjects in Cornerstone versus those in TAU. We will likewise examine whether within person changes in the proposed mediating variables differ across intervention groups.

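### The 80% power for d = 0.73 assumes all 60 participants are analysed, while the protocol plans a final sample of 55, at which power is about 76%

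*Protocol article*

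**What the plan says.** Three places in the protocol article bear on this point.

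- **Randomization and sample.** The recruitment target is 60: "We will recruit 60 transition-age youth with SMHC and approximately 20 stakeholders". The power statement takes all of them as analysed: "with our sample size of 30 per group we will have" "80 % power with *p* = 0.05 to detect a large effect", with the effect given as Cohen's d = 0.73. The same section calls the testing exploratory and attributes the modest sample size to the limits of the grant mechanism.
- **Enrollment, retention, and tracking.** The protocol makes its own allowance for loss: "We are recruiting 60 transition-age youth (TAY) to achieve a final sample size of 55".
- **Analysis (aim 2).** For each participant the end-of-study value minus the baseline value is calculated for each outcome, and a simple t "test will be used to assess whether these changes differ across treatment conditions". The worked example uses the 9-month assessment.

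**The concern.** Two sections that follow one another use different sample sizes. Power is stated for 60 analysed, and the retention plan is for 55. The analysis is a comparison of change scores, so anyone who misses the final assessment has no change score to enter. The article names no method that would bring the missing five back into the t test. The sample that counts for power is therefore the planned 55, and the stated 80% for d = 0.73 does not belong to it.

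What is at stake is limited. This is the only power or precision figure in the article, and the data are meant to inform a later, fully powered trial. A reader who takes d = 0.73 as the effect the trial could detect with 80% power would take a value that is slightly too small.

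**Working it through.** **Inputs**

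- Recruited: 60, as 30 per group (Randomization and sample).
- Effect: d = 0.73; significance level 0.05; stated power 80% (same section).
- Planned final sample: 55 (Enrollment, retention, and tracking), a planned loss of 5/60 = 8.3%.
- Test: two-sample t test on change from baseline (Analysis).
- Assumed, because not stated: a two-sided test, and a split of the 55 as 28/27.

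**Formula**

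For group sizes n1 and n2, the t test has df = n1 + n2 − 2 and noncentrality δ = d × √(n1·n2/(n1 + n2)). Power is the probability that a noncentral t variable with these parameters falls beyond ± the two-sided 5% critical value. The detectable effect is the d at which this probability is 0.80.

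**Step 1: reproduce the stated figure (30/30)**

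- √(900/60) = 3.873, so δ = 0.73 × 3.873 = 2.827; df = 58; critical value 2.002.
- Power = 79.4%. The normal approximation gives 80.7%.
- Effect detectable with 80% power: d = 0.736 (0.723 by the normal approximation).

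The plan's 80% is reproduced after rounding. A one-sided 5% test would give 87.5%, so a two-sided test is the reading that fits.

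**Step 2: repeat at the planned final sample (28/27)**

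- √(756/55) = 3.707, so δ = 0.73 × 3.707 = 2.706; df = 53; critical value 2.006.
- Power = 75.7%.
- Effect detectable with 80% power: d = 0.770.

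**Step 3: sensitivity to the assumptions**

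| Analysed | Method | Power at d = 0.73 | d for 80% power |
|---|---|---|---|
| 30/30 | noncentral t | 79.4% | 0.736 |
| 28/27 | noncentral t | 75.7% | 0.770 |
| 28/27 | normal approximation | 77.2% | 0.756 |
| 30/25 (all loss in one group) | noncentral t | 75.4% | 0.773 |

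Put all five losses in one group and power falls by only a further 0.3 points. The normal approximation shows a drop of similar size, from 80.7% to 77.2%.

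**Size of the gap:** 79.4 − 75.7 = 3.7 percentage points of power. In detectable effect it is 0.770 − 0.736 = 0.034 against the recomputed value, or 0.770 − 0.73 = 0.04 against the stated one.

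**The case against.** The strongest defence is that the sentence is conditional on 30 per group and is right on that condition. The protocol also says plainly that testing is exploratory, that the grant mechanism set the sample size, and that formal outcome testing is not usually recommended in a pilot like this. No decision rule depends on the power figure. All of this stands, and it is why the point is minor. It does not remove the mismatch, because the sentence says what the trial will have while the next section plans for fewer participants. Nor does the intention-to-treat design help. It means that data collection continues for people who leave the programme; the planned final sample is still 55.

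A reader might infer more than the document supports:

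- **That the 30/30 calculation is itself wrong**, because the noncentral t gives 79.4% and not 80%. That is rounding.
- **That 55 contradicts the cited retention rate**, since 60 × 0.90 = 54. The protocol says "Our strategies have resulted in high retention rates (90 %) in our previous studies", which is a historical rate, and then gives reasons to expect few losses here. Nothing says that 55 was calculated from 90%.
- **That leaving the scale of d unstated is an error.** The planned test is on change scores, so d is naturally in standard deviations of the change. Converting it to outcome standard deviations needs a baseline-to-follow-up correlation, which the document does not give.
- **That poor power for a moderate effect is a fault.** The protocol claims power only for a large effect.

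**Conclusion.** The point holds as a minor correction of a stated figure. The 80% power for d = 0.73 applies only if all 60 participants supply an end-of-study score. At the protocol's own final sample of 55, power for that effect is about 76%, and 80% power is reached at about d = 0.77.

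This rests on a two-sided 5% test, a near-equal split of the 55, and analysis of only those participants who have a change score. The first is supported by the reproduction of the plan's figure, and the second hardly affects the result.

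A reader might go on to infer that the design is underpowered for its purpose or that more participants are needed. The document does not support that: the stated primary goal is to gather feasibility and acceptability data, and the conclusion that only a large effect is detectable is the same at d = 0.73 and d = 0.77.

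**What to change.** Restate the power sentence under Randomization and sample at the planned final sample, for example: *With 55 participants analysed (60 enrolled), a two-sided 5% t test on change from baseline has 80% power for d = 0.77 (about 76% for d = 0.73).* This also states the sidedness and the variable tested.

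The cost is one sentence and a slightly less favourable number. No participants are added, and no procedure or analysis changes.
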